## Abstract

**Background:**

There is limited evidence regarding the outcomes and impacts of Patient and public involvement (PPI) in research, mainly based on narrative studies. Existing frameworks for supporting and evaluating PPI often require adaptation to specific contexts, and comprehensive instruments are needed. From an international perspective, strengthening the scientific foundation that underpins PPI is crucial to generate stronger evidence to understand which approaches work best, in which contexts, and with what effects.

**Objectives:**

To promote PPI implementation in German health research, this project aims to (1) Establish an evaluation framework, (2) Develop a modular evaluation tool in the form of a questionnaire and (3) Pilot and psychometrically validate the tool.

**Methods and analysis:**

A three-phase mixed methods approach will be employed, integrating qualitative and quantitative data. First, we will explore with researchers, research partners and other stakeholders in health services research what contributes to meaningful and successful PPI through a web-based survey and focus groups. Findings are discussed in a codesign workshop in which participants agree on an evaluation framework based on a LOGIC model. Second, items from international instruments that evaluate PPI are deductively assigned to the evaluation framework. Further items are developed based on the focus groups from phase 1. Cognitive pretests and qualitative review will be conducted with researchers and patients in order to refine the item pool and develop the evaluation tool. Third, the evaluation tool with modules for researchers and patients will be piloted in a web-based survey. Data analysis will include thematic analysis for qualitative data and descriptive and psychometric analyses for quantitative data. A participatory research team will provide ongoing support throughout all project phases.

**Ethics and dissemination:**

Ethical approval has been obtained from the Local Ethics Committee of the Centre for Psychosocial Medicine, University Medical Centre Hamburg-Eppendorf (LPEK-0889). The study will follow the principles of the Helsinki Declaration and good scientific practice. Results will be disseminated at national and international conferences, public symposiums and in peer-reviewed journals, contributing to the internationally developing field of PPI in research and addressing relevant research gaps.

STRENGTHS AND LIMITATIONS OF THIS STUDYThis study employs a mixed methods approach, integrating qualitative (eg, focus groups, cognitive pretests) and quantitative (eg, surveys, psychometric validation) methods.It involves multiple stakeholders, including researchers, research partners and patients, to ensure comprehensive insights and participatory development of the evaluation framework and modular tool.It addresses the lack of comprehensive frameworks for evaluating patient and public involvement (PPI) in German health research, providing essential tools to support, report and systematically assess the impacts of PPI.

## Background

Through patient and public involvement (PPI) in research, the knowledge, skills and expertise of those directly affected by health issues and/or research outcomes can be considered. Especially in the UK, the US and Canada, it is widely accepted that involving patients and the public in various roles^1^ is possible at all stages of the research process.^2^ They can prioritise research questions, assist during study implementation, review and interpret study results, and contribute to the dissemination of findings.^3^ As a consequence, funders, policy‐makers and research organisations increasingly expect patients to be involved, particularly in health services research.

There are specific national programmes that support PPI by promoting and providing infrastructure. In the UK, support was initially provided by INVOLVE, a national advisory group funded by the UK government. INVOLVE has since been integrated into the National Institute for Health and Care Research (NIHR) and its functions are now part of broader NIHR initiatives. In the USA, the government-sponsored Patient-Centred Outcomes Research Institute (PCORI) strengthens patient and stakeholder relationships by building networks. Moreover, PCORI guides and supports PPI within the research it funds. In Canada, the Institutes for Health Research Strategy for Patient-Oriented Research (acts as a funder and facilitator for PPI in research. Beneficial as well as challenging outcomes and impacts of PPI have been demonstrated. Systematic reviews^4^ and umbrella reviews^5^ suggest that researchers report a greater understanding and deeper insights into their research area as well as personal benefits such as motivation. Challenges include feeling uncomfortable sharing power over research and investing additional time in partnerships.^4 5^ Patients, on the other hand, report benefits including increased knowledge and skills, a more positive attitude towards research, improved access to information and personal benefits such as feeling empowered. However, patients also reported feelings of not being listened to or taken seriously by researchers, as well as feeling overwhelmed by tasks and responsibilities during the research process.^4 5^ In terms of outcomes and impacts on the research process, PPI can lead to more patient-centred research questions. Moreover, the comprehensibility of patient information material, questionnaires and interview schedules may be improved. PPI also accounted for more appropriate recruitment strategies and enhanced implementation and dissemination.^6 7^ Additionally, PPI may improve the health-related outcomes of the involved patients.^8^ Challenges regarding the organisation of research projects reflect the additional time required and the insufficient financing of PPI.^7 9^ Most of the reported outcomes and impacts originate from narrative studies. As a consequence, the evidence base in PPI concerning the outcomes, impact and good practice criteria is rather limited.^4 5 7 9 10^

There are several reasons why adequate evidence has not been generated thus far:

First, some researchers do not see a need to generate evidence on the outcomes and impacts of PPI, as they see it as a democratic right with intrinsic value.^10^ The international debate on the need to measure the outcomes and impact of PPI is ongoing.^11^ For example, Staley and Barron emphasise that PPI supports mutual learning between patients and researchers and does not require measuring its impact.^12^ In contrast, Staniszewska points out that measuring outcomes and impacts strengthens the evidence base of PPI.^13^ Boivin *et al* further emphasised that meaningful involvement requires sound evaluation.^14^ However, a compromise is that PPI evaluation should not be limited to measuring outcomes and impacts, but should also include the process and context.^10^ Second, there is a heterogeneous terminology^5^ and a poor reporting of PPI,^7 8 15 16^ limiting the detection of its outcomes and impacts. Recently, consensus-informed guidelines for reporting PPI in research (Guidance for Reporting Involvement of Patients and the Public; GRIPP2) have been published on the EQUATOR webpage (www.equator-network.org). The GRIPP2 includes minimum reporting requirements in a short form.^17^ In addition to defining the aims related to PPI and the methods used, articles and reports should also include impacts and outcomes—positive as well as negative—along with their measurement. While challenges such as tokenistic PPI may still exist,^18^ this improves the quality, transparency and consistency of PPI reporting.^19^ Third, there are numerous frameworks for supporting PPI in research.^11^ A comprehensive review and synthesis of PPI frameworks identified five different types: power-focused, priority-setting, study-focused, report-focused and partnership-focused frameworks. It also revealed that most published frameworks are rarely used outside the groups that developed them. Therefore, the authors concluded that these frameworks are difficult to transfer to other contexts and require adaptation for specific settings.^11^ Fourth, available tools for evaluating PPI do not take into account its complexity, as both the process and the context need to be described. Furthermore, outcomes and impacts on patients, researchers and the research itself need to be considered.^20^

There is an increasing number of tools available for evaluating PPI.^21^ For example, the Public Involvement Impact Assessment Framework (PiiAF) aims to help researchers plan and assess the impacts of PPI. It compiled a set of questions on the values, approaches, focus, study design and impacts. PiiAF can assist in documenting the quality of PPI in research projects.^22^ It can be tailored to specific projects, but there are no defined items. PCORI uses different templates to collect information about PPI from researchers^23^ and patients.^24^ Stocks *et al*
25 developed an instrument to evaluate PPI from the patient’s perspective focusing on the quality of involvement.^26^ The instrument accounts for both personal (eg, feeling valued, achieving goals, feeling empowered) as well as contextual factors (eg, research participation, previous experience). Outcomes and impact on the research process are only implied.^26^ The Public Patient Engagement Evaluation Tool (PPEET)^27^ evaluates its quality, including four principles: integrity of design and process, influence and impact, participatory culture, collaboration and common purpose. Different versions for researchers and patients are available. Another Canadian instrument, the Patient Engagement In Research Scale (PEIRS), is one of the very few instruments that underwent psychometric evaluation.^28 29^ The items reflect procedural requirements, convenience, contributions, team environment and interaction, support, feelings of being valued and benefits. While the PiiAF lacks standardisation, the WE-ENACT tools do not account for the context. Similarly, the instrument by Stocks *et al*
25 and the PPEET^27^ fails to include information on how PPI is conducted. The PEIRS^28 29^ does not encompass the perspective of researchers.

To date, none of these tools provides a comprehensive evaluation of PPI with regard to the context, process, outcomes or impacts from different perspectives. Moreover, their scientific rigour in the development and validation process requires improvement.^21^ In summary, from an international perspective, there is a need to strengthen the science behind PPI to generate stronger evidence to understand which PPI approaches work best, in which contexts and with what effects.^16 21 30–35^ In addition to these general methodological aspects, country-specific contexts must also be considered. The implementation of PPI is heterogeneous. For example, in Germany, PPI has not yet been systematically implemented in health services research. Among the 683 studies (published up to 2009) included in the extensive review on PPI conducted by Boote *et al*
36 only two originated from Germany. This has not changed over the past decade. In 2021, Biddle *et al* concluded that the implementation of PPI is very heterogeneous and not yet firmly established or formalised in European health services research. They refer to a lack of infrastructure, guidance and support as potential barriers.^37^

Recently, German research funders have introduced PPI into health research as a requirement within project proposals, aiming to drive its practice. Meanwhile, some documents and principles have been published that provide orientation for participatory health research in Germany.^38–42^ However, despite these important contributions, a comprehensive and systematic framework for evaluating PPI in health service research in Germany remains absent. The lack of an overarching evaluation concept may risk tokenistic approaches to PPI, as we have learnt from international research.^19 43 44^ Therefore, an evaluation framework for PPI is needed to adequately support, report and evaluate PPI^11^ in health services research in Germany. Furthermore, while realising PPI has been central in various of our previous studies,^45–50^ we were also confronted with the lack of adequate instruments to evaluate the process, perceived impact and potential harms of PPI. Thus far, there is a limited understanding of what constitutes meaningful and successful PPI from the perspectives of both researchers and patients in health services research in Germany.

## Objectives

Therefore, the study objectives are (1) To establish a theoretical evaluation framework, (2) Based on this, to develop a modular evaluation tool as a practical questionnaire for various stakeholders and (3) To pilot the modular evaluation tool including psychometric testing.

We would like to prepare an evaluation framework for PPI in health services research in Germany, considering the context, process, outcomes and impacts. The objective of establishing an evaluation framework is related to the following research questions:

What does meaningful and successful involvement in health services research look like for researchers and patients in Germany?How should the evaluation of PPI be approached in health services research in Germany?

We will acknowledge the international literature and will explore the specifics of PPI in health services research in Germany. Items will be devised acknowledging existing instruments as well as qualitative survey and interview data. Related research questions are:

Do the devised items address the consented evaluation framework?Are the devised items of the modular evaluation tool comprehensive and relevant?

The developed modular evaluation tool will undergo validity and reliability testing.

Does the modular evaluation tool produce stable and consistent results?

We will place further emphasis on PPI in the evaluation design and reporting by involving a participatory research team in all phases of the research process.

## Methods and analysis

### Study design

The proposed 3-year mixed-methods project comprises three phases. Each phase examines one of the objectives described above (figure 1).

**Figure 1 F1:**
[figure not shown]
Overview of the study design.

### Study population

The study will focus on the perspectives of researchers, patients and stakeholders with PPI experience within the context of German health services research. Adult patients (≥18 years) with lived experience in treatment-relevant health conditions and experience with the healthcare system will be included. Patients with limited proficiency in the German language, as well as those with severe impairments (eg, cognitive impairment or lower quality of life due to illness), will be excluded. Researchers and patients will be recruited through databases on publicly funded health services research and via recently established PPI networks (eg, Deutsches Netzwerk Versorgungsforschung (DNVF) patient advisory board, personal contacts). Detailed information regarding specific study population and recruitment strategy will be provided aligning with the description of the three phases and work packages presented below.

#### Relevance of sex, gender and/or diversity

Special attention will be given to considering the diverse perspectives of researchers and patients. In web-based surveys, researchers and patients with relevant experiential knowledge about patient involvement can contribute. The community of health services researchers in Germany is heterogeneous,^51^ but diversity has not been investigated thus far. Patients involved in this research are often white, female and retired.^52^ It is therefore likely that, in aiming to engage individuals and community groups already experienced in participatory research, participating patients may have a narrow set of sociodemographic characteristics, and the views of a more diverse population may be underrepresented. We will include diversity aspects in questions regarding sociodemographic characteristics and will therefore be able to at least describe them in the survey sample. Setting up a web-based survey will not produce selection bias among researchers. However, patients who have previously been involved in research will presumably be familiar with the technique.

For the qualitative study parts, we will stratify our sampling strategies based on relevant sociodemographic aspects to reflect diversity. We will sample researchers with regard to gender, age/research stage and the field of expertise/research methods. With regard to patients, we consider gender, age and education to be relevant. In addition, we will include patients with different health conditions and associated networks (individual patient vs member/representative in a patient organisation). By asking for sociodemographic characteristics, we will be able to report on diversity in the qualitative study parts.

Moreover, we aim to identify a diverse group of people, by gender, age and educational background, to join the PPI group that we are calling the participatory research team. This team should also include experience with different kinds of diseases and networks as well as experience with being a patient partner. On the one hand, we assume that patient partners acquire knowledge that is useful for future participatory research teams.^53 54^ On the other hand, we will recruit additional persons without prior experience in PPI. We assume that skills such as confidence in articulating oneself in a formal meeting would support an interest in joining a participatory research team. As suggested by Thompson *et al*
53 and Lander *et al*,^55^ we will reflect on which input will be most useful, provide reasons for why certain participants were selected and discuss how potential recruiting and representativeness limitations impact the process and results.

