##### Web-based survey

The web-based survey consists of different modules for researchers and patients. They will be recruited through several time-shifted strategies: (a) Identification and invitation of principal investigators of publicly funded health services research, (b) Identification and invitation of researchers and patients (or their representatives) involved in publicly funded health services research that implements PPI and (c) Through personal knowledge (eg, DNVF), including its patient advisory board).

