#### Recruitment and procedures

Principal investigators of publicly funded projects in the field of health services research (German Research Foundation (Deutsche Forschungsgemeinschaft, DFG), Federal Ministry of Research, Technology and Space (Bundesministerium für Forschung, Technologie und Raumfahrt, BMFTR), Federal Ministry of Health (Bundesministerium für Gesundheit, BMG), innovation fund of The Federal Joint Committee (Gemeinsamer Bundesausschuss, G-BA) can be identified using databases (eg, funded projects information system (GEPRIS), funding catalogue of the BMFTR). The inclusion criteria specify that the project must be conducted in Germany, initiated in 2010 or later, and aimed to gain knowledge about healthcare. In the GEPRIS Database, 78 researchers are currently listed, while the BMBF funding catalogue contains 571 projects. Researchers will be contacted via email and invited to participate in a linked web-based survey. With regard to sampling strategy 2, these principal investigators can name further researchers and patients for participation in the survey. Four weeks after the second reminder email has been sent to the principal investigators, sampling strategies (b) and (c) will be applied. Links to the web-based survey will be sent via email. Two reminders will be sent.^57^ The web application Research electronic data capture (REDCap) will be used to implement the web-based survey.^58^ Informed consent will be obtained online.

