In module B, all participating principal investigators and researchers and patients will provide information on individual characteristics. Researchers will answer questions on age, gender, seniority^19^ and patients will be asked questions with regard to age, gender, health condition with lived experience and membership of self-help organisation. In module C, the participants are presented with information on PPI and will be asked to rate different elements of the frameworks for supporting PPI in research according to their relevance.^11 38–41^ For both aspects, a nine-point Likert scale (1=not relevant; 9=very relevant) will be used. In addition, open-ended questions will be asked about whether any relevant aspects are missing. At the end of the web-based survey, participants can consent to be contacted for further interviews or surveys in the project, which requires storing their email address and further details (such as project and investigator characteristics) in a project database and/or for receiving information about the project results.

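### The web survey is said to be free of selection bias among researchers, but opt-in, nomination and personal-contact recruitment support that only for web coverage; the listed patient items also omit education

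*Protocol article*

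**What the plan says.** The section on sex, gender and diversity makes two statements about the web surveys. On researchers: "Setting up a web-based survey will not produce selection bias among researchers". The next sentence turns to patients: "patients who have previously been involved in research will presumably be familiar with the technique". On diversity, it says that such aspects will be asked about and that the team "will therefore be able to at least describe them in the survey sample".

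Phase 1 recruitment is set out under Web-based survey and its Recruitment and procedures:

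- Strategy (a): principal investigators are identified from funding databases, and "Researchers will be contacted via email and invited to participate in a linked web-based survey".
- Strategy (b): researchers and patients "involved in publicly funded health services research that implements PPI" are approached; in this connection "these principal investigators can name further researchers and patients for participation in the survey".
- Strategy (c): people are reached through personal contacts.

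The Phase 3 pilot again adds snowball sampling and personal contacts.

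Module B asks researchers about age, gender and seniority. For patients, "patients will be asked questions with regard to age, gender, health condition with lived experience and membership of self-help organisation". The Phase 1 Data analysis section summarises the module C relevance ratings by median, mean and SD, and presents the result as how health services researchers in Germany see the domains.

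**The concern.** The first statement has no qualifier. Choosing the web as the mode settles who can reach the questionnaire. It does not settle who answers, or whom a principal investigator chooses to name. People who care about PPI may be readier to answer a survey on PPI, and nomination then adds a second layer of selection. The article describes no comparison of respondents with the invited frame and no reporting by recruitment route.

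At stake is the interpretation of the ratings. Strategy (a) invites principal investigators of publicly funded projects without requiring PPI, and the conclusion is worded for health services researchers in general. If response depends on PPI attitude, the ratings describe a more PPI-minded group than the one named. The condensed survey results also open the codesign workshop that sets the framework.

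The second issue is smaller. The section calls education relevant for patients in the qualitative parts, and the focus groups are to vary in educational background. Survey participants who agree to further contact are one source for those groups, yet education is not among the listed patient items.

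**Working it through.** The protocol gives no response rate or expected rating, so there is no figure to reproduce. It gives frame counts for two funding sources (78 researchers and 571 projects), but these say nothing about who replies. The check is a comparison of the text, followed by an illustration with assumed inputs.

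**1. Recruitment route against the no-selection-bias statement**

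| Route | What decides inclusion | Can it depend on PPI attitude or experience? |
|---|---|---|
| (a) Email to principal investigators | Willingness to answer | Yes |
| (b) Projects implementing PPI, nomination | PPI practice; the nominator's choice | Yes, by construction |
| (c) Personal contacts | Being known to the team or network | Yes |
| Phase 3 snowball and personal contacts | Onward referral; being known | Yes |

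No route makes response independent of PPI attitude. Web mode bears only on access.

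**2. Bias in a mean rating**

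Let r be the response rate and D the respondent mean minus the non-respondent mean. The respondent mean differs from the mean of everyone invited by

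bias = (1 − r) × D.

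Assumed ranges: r from 10% to 50%, D from 0.5 to 2 points on the nine-point scale.

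| r | D = 0.5 | D = 1 | D = 2 |
|---|---|---|---|
| 10% | 0.45 | 0.90 | 1.80 |
| 20% | 0.40 | 0.80 | 1.60 |
| 30% | 0.35 | 0.70 | 1.40 |
| 50% | 0.25 | 0.50 | 1.00 |

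The range is 0.25 (0.50 × 0.5) to 1.8 (0.90 × 2). If D = 0, the bias is zero at any response rate.

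**3. Composition of the respondents**

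Let p be the share of invited researchers with PPI experience, responding at rate a, while the others respond at rate b. Their share among respondents is p·a / [p·a + (1 − p)·b]. With p = 30% (assumed):

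- a = b = 30%: 0.09 / (0.09 + 0.21) = 30%, unchanged.
- a = 40%, b = 20%: 0.12 / (0.12 + 0.14) = 46%.
- a = 40%, b = 10%: 0.12 / (0.12 + 0.07) = 63%.

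**4. Diversity items**

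For patients in the qualitative parts, the diversity section names five characteristics: gender, age, education, health condition and network (individual or patient organisation). Module B lists age, gender, health condition and self-help membership. Four of the five therefore have an item, and education has none.

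**The case against.** **The sentence is about survey mode.** It is followed by a remark on patients' familiarity with the technique, so the authors probably mean that a web format excludes no researcher. That reading is likely and should be granted. A reader might infer that the authors deny self-selection altogether, and the context does not establish that intention. But the sentence does not state the limit, and the section's concession about narrow representation covers patients only. The later promise to discuss representativeness follows the text on the participatory research team and does not clearly reach the survey.

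**PPI-experienced people are the target.** The Study population section says so, and strategy (b) is openly restricted to PPI projects. Some over-representation is therefore by design. This stands in part: strategy (a) invites principal investigators generally, and the analysis section describes the view of health services researchers without that restriction.

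**The consequence is small.** The ratings are descriptive, no cut-off is applied, and the framework is settled by themes, voting and consensus. A uniform shift would leave the order of the elements unchanged. This lowers the stakes. It does not remove them, since a shift need not be uniform across elements.

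**The item list comes from a condensed article.** Modules B and C are described but no module A, and project characteristics are also analysed, so a missing item on researchers' field is not shown. The Phase 3 list is explicitly open. The protocol ties education to the qualitative parts and the participatory research team, not expressly to the survey. These points stand and confine the second issue to education in the Phase 1 patient list.

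**Conclusion.** The statement is unsupported as written. It is defensible for web-mode coverage and for nothing wider. The protocol's own recruitment lets response depend on PPI attitude or experience, while the ratings are presented as the view of the whole research community. The size is unknown: 0.25 to 1.8 points under the assumed ranges, and zero if response is unrelated to the ratings. Every response rate and difference used here is an assumption.

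Three stronger conclusions might be inferred and are not supported:

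- That the ratings are biased by some particular amount. The documents give nothing from which to estimate it.
- That diversity cannot be described. The promise concerns the achieved sample, which can be described on age, gender, seniority, health condition and self-help membership whatever the response pattern.
- That the focus groups cannot be stratified by education or field. Those who agree to further contact leave an email address, and the qualitative parts will ask for sociodemographic characteristics, so either can be asked at that stage.

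The education gap is therefore a mismatch between the diversity aims and the listed items that is worth closing. Ethnicity and retirement appear only as background on who tends to be involved; the protocol does not promise to measure them.

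**What to change.** 1. Limit the sentence to coverage by web mode, or delete it, and state self-selection and nomination as limitations of the surveys.
2. Report invitations, responses and module C ratings separately for directly invited participants and for nominated or personally recruited ones.
3. Compare responding projects with the invited frame on fields that the funding databases hold, for example funder and start year. The inclusion criteria already use both, and the survey already analyses project characteristics; confirm that these two fields are among them so that an aggregate comparison is possible.
4. In the Phase 1 Data analysis section, attribute the ratings to responding researchers.
5. Add education for patients to module B, or restrict the diversity promise to the listed characteristics.

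The cost is one survey question, one descriptive table and a more modest claim. If the survey has already opened, items 1 to 4 can still be made, provided recruitment route and the project fields were recorded.
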